### Randomization, Allocation Concealment, and Blinding

A random allocation sequence will be generated by an independent, blinded statistician using research randomizer (http://www.randomizer.org). Sequentially numbered, opaque, sealed envelopes (SNOSE) are used to achieve allocation concealment. One research member will independently allocate the participants to groups in a 1:1 ratio by opening the envelopes sequentially. The primary and secondary outcomes will be assessed by researchers blinded to the group allocations.

### Intervention

Clinical evaluation will be conducted before each rehabilitation training session. Those who pass the following evaluation will enter the rehabilitation program: no onset or recurring chest pain in the past 8 h; no onset symptoms of decompensated heart failure; new onset arrhythmia or dynamic changes of electrocardiogram (ECG) in the past 8 h; no further elevation in troponin levels; resting heart rate <110 beats per minute, resting blood pressure (BP) 90–150/60–100 mmHg and blood oxygen saturation (SaO_2_) ≥95%. Then, physical fitness assessments will be performed before rehabilitation program which include lung function, grip strength, maximum strength, flexibility, coordination, and balance. Additionally, assessment of anxiety and depression using Patient Health Questionnaire−9 (PHQ-9) and Generalized Anxiety Disorder−7 Questionnaire (GAD-7) will be evaluated before rehabilitation program.

In control group, subjects without contraindications will receive air pressure therapy to prevent deep vein thrombosis. The impedance cardiography (ICG) is a reliable, repeatable and non-invasive method to monitor cardiodynamic data including stroke volume (SV), end diastolic filling rate (EDFR) and peripheral vascular resistance (SVR) (20, 21). Passive Leg Raising (PLR) test, a reversible fluid-loading procedure to test fluid responsiveness, is used to ensure the safety of phase I cardiac rehabilitation (22, 23). Patients randomized to the CR group will start the exercise program if the PLR test is positive. Optimized treatment will be taken in patients with negative result of the PLR test. CR program will be started once the PLR test turn to positive in this part of patients. Personalized CR training will be performed based on the state of mind, New York Heart Association (NYHA) classification and physical fitness assessments. Whether the subjects will enter into the next level training program is according to the heart rate response, Borg scale score and Perme score (Table 1). A rehabilitation therapist will closely monitor the ECG, BP, SaO_2_, and ICG parameters (SV, EDFR, and SVR) at the bedside during the rehabilitation exercise training. Rehabilitation training will be stopped if the following situations occur: new onset arrhythmia or heart rate rise ≥20 beats per minutes or dynamic changes of ECG; systolic BP drops or rises more than 40 mmHg; SaO_2_ < 95%; a continuous downward trend in SV more than 1 min; onset symptoms of exercise intolerance such as chest tightness, heart palpitations, and dyspnea.

**Table 1 T1:** Personalized cardiac rehabilitation program.

	**Level**	**Level 1**	**Level 2**	**Level 3**	**Level 4**	**Level 5**	**Level 6**	**Level 7**
Assessment	Unconscious	Unconscious	Conscious	Conscious	Conscious	Conscious	Conscious	Conscious
	Muscle strength	Upper limb muscle strength <3 level	Upper limb muscle strength ≥3 level	Limb muscle strength ≥ 3 level	Limb muscle strength ≥4 level	Limb muscle strength ≥4 level	Lower limbs muscle strength 5 level	Lower limbs muscle strength 5 level
	NYHA classification	III–IV	III–IV	III	II–III	II–III	II–III	II–III
Rehabilitation plans and programs	Breath training	/	/	Progressive breathing muscle training	Progressive breathing muscle training	Progressive breathing muscle training	Progressive breathing muscle training	Progressive breathing muscle training
	Range of Motion (ROM)	Passive rom once per day	Active/passive rom once per day	Active rom once per day	Active rom once per day	Active rom once per day	Active rom once per day	Active rom once per day
	Treadmill training	Passive bed treadmill training for 10–20 min	Passive bed treadmill training for 10–20 min	Bed treadmill training for 10–20 min	Bedside treadmill training for 10–20 min	bedside treadmill training for 10–20 min	Bedside treadmill training for 10–20 min	Bedside treadmill training for 10–20 min
	Resistance training	/	/	Progressive resistance training 15 times per group (elbow flexion and extension movements), 3 groups, rest for 2 min between each group	Progressive resistance training 15 times per group (elbow flexion and extension movements for 3 groups and abdominal crunch for 1 group and hip bridge for 1 group), rest for 2 min between each group	Progressive resistance training 15 times per group (elbow flexion and extension movements for 3 groups and abdominal crunch for 1 group and hip bridge for 1 group), rest for 2 min between each group	Progressive resistance training 15 times per group (elbow flexion and extension movements for 3 groups and abdominal crunch for 1 group and hip bridge for 1 group), rest for 2 min between each group	Progressive resistance training 15 times per group (elbow flexion and extension movements for 3 groups and abdominal crunch for 1 group and hip bridge for 1 group), rest for 2 min between each group
	Sitting in bed (bed head elevation >45°)	/	Sitting in bed 5 min, 2 times per day	Sitting in bed 5 min, 2 times per day	Sitting in bed 5 min, 2 times per day	Sitting in bed 5 min, 2 times per day	Sitting in bed 5 min, 2 times per day	Sitting in bed 5 min, 2 times per day
	Sitting at the edge of the bed	/	/	Sitting at the edge of the bed 5 min, 2 times per day	Sitting at the edge of the bed 5 min, 2 times per day	Sitting at the edge of the bed 5 min, 2 times per day	Sitting at the edge of the bed 5 min, 2 times per day	Sitting at the edge of the bed 5 min, 2 times per day
	Standing and stepping	/	/	/	Standing/stepping for 2 min	Standing/stepping for 2 min	Standing/stepping for 5 min	Standing/stepping for 5 min
	Bed to chair transfer	/	/	/	Sitting in chair 5 min per day, 2 times per day	Sitting in chair 5 min per day, 2 times per day	Sitting in chair 5 min per day, 2 times per day	Sitting in chair 5 min per day, 2 times per day
	Walking bedside bed	/	/	/	/	Walking training by supported by walker for 2 min	Walking training beside bed for 2 min	Walking training for 2 min
Goal	Heart rate response (compared with resting heart rate)	Increase 5–15 beats per minute	Increase 5–15 beats per minute	Increase 20–30 beats per minute	Increase 20–30 beats per minute	Increase 20–30 beats per minute	Increase 20–30 beats per minute	Increase 20–30 beats per minute
	Borg scale score		<12	12–13	12–13	12–13	12–13	12–13
	Perme score	/	Sitting up on bed for a score of 3	Meditation balance for a score of 3	Sit-to-stand transfer or standing balance for a score of 3	Bed to chair transfer for a score of 3	Walking training for a score of 3	/

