**Methods:**

This is a single-center, randomized controlled, single-blind clinical trial. A total of 120 participants hospitalized in CICU with ADHF will be randomly allocated in the ratio of 1:1 to two groups: CR group and control group. Participants will receive tailored and progressive CR intervention or attention control. The CR intervention include personalized breathing training, small muscle group resistance training, and aerobic endurance training based on the physical fitness assessment results. The subjects will receive the CR training for 5 days and will be followed up for 6 months. The primary endpoints are the score of the short physical performance battery (SPPB) and 6-month all-cause rehospitalization. The secondary endpoints include cardio-pulmonary function, activities of daily living (ADL), in-hospital mortality rate and 6-month all-cause mortality rate.

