### Inclusion Criteria

(1) Age ≥ 18 years old;

(2) Acute decompensated heart failure was defined according to the “2021 ESC Guidelines for the diagnosis and treatment of acute and chronic heart failure” (13). Combined with symptoms, signs and laboratory results, and meet all the following conditions:

(2.1) At least one symptom was worsened from baseline: (a) dyspnea (dyspnea after exercising, paroxysmal nocturnal dyspnea or orthopnea), (b) venous congestion of systemic circulation (edema of lower extremities, liver congestion, ascites), and (c) tissue hypo-perfusion (oliguria or anuria, cold clammy limbs, consciousness disorder, hyper-lacticacidemia, or metabolic acidosis);

(2.2) At least one of the following signs of heart failure: (a) pulmonary edema on exam or by chest X ray, (b) Increased b-type natriuretic peptide or N-terminal prohormone BNP, and (c) abnormal cardiac structure and/or function by cardiac ultrasound;

(3) The symptoms and signs are consistent with acute decompensated heart failure judged by the investigator;

(4) Patients who have New York Heart Association Cardiac Function class III or IV symptoms at admission;

(5) Clinical stability has been achieved for 24 h after optimizing treatment;

(6) Patient was independent with basic activities of daily living including the ability to ambulate independently (with or without the use of an assistive device) prior to admission.

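### Entry criteria do not match the readiness and PLR conditions for starting exercise, so eligible patients can be randomised to CR and train late or never

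*Protocol article*

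**What the plan says.** **Entry.** Inclusion criterion 5 reads "Clinical stability has been achieved for 24 h after optimizing treatment". Neither criteria list gives a limit for heart rate, blood pressure, oxygen saturation or troponin, and neither mentions a PLR result. There is some overlap with the later readiness list: exclusion 1 covers chest pain within 8 h, and exclusion 2 covers certain arrhythmias.

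**Readiness check.** The Intervention section states: "Clinical evaluation will be conducted before each rehabilitation training session. Those who pass the following evaluation will enter the rehabilitation program". Among the conditions are "resting heart rate <110 beats per minute, resting blood pressure (BP) 90–150/60–100 mmHg", a saturation floor and no further troponin rise. The text does not say whether the first such check comes before or after randomisation, and it names no arm.

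**PLR condition.** The same section then says: "Patients randomized to the CR group will start the exercise program if the PLR test is positive". Patients with a negative test have treatment optimised, and "CR program will be started once the PLR test turn to positive in this part of patients". No latest start is given.

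**Window.** The abstract says: "The subjects will receive the CR training for 5 days and will be followed up for 6 months". Study Design also describes a 5-day intervention period.

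**Losses.** Exclusion 12 lists patients who drop out or are discharged while the study is running, which can only be applied after entry. Sample Size allows for 20% drop-off and 7% missing data. It makes no separate allowance for CR patients who stay in the trial but are not trained.

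**The concern.** A check attached to training sessions can bind only the arm that has sessions, and the PLR condition is worded for that arm alone. Two comparable patients who both meet every entry criterion are therefore treated differently after allocation. The one in CR may wait for, or never receive, the intervention. The one in control faces only the contraindications to air pressure therapy.

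There are two possible consequences, depending on how non-starters are handled.

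- **Kept in the CR arm.** The comparison stays unbiased for the effect of offering CR, but it is diluted on both primary endpoints. The sample size was not built for this. Its planning values come from an earlier rehabilitation trial in older ADHF patients which, according to the Introduction, excluded patients admitted to intensive care. Those values cannot be presumed to reflect non-starting in a CICU population.
- **Removed.** Exclusion 12 offers a route. The CR arm would lose patients who fail stability-type conditions while control keeps their counterparts. That favours CR on SPPB, rehospitalisation and mortality, and extra patients do not cure it.

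**Working it through.** **1. Compare entry with the start conditions.**

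| Start condition (Intervention) | Counterpart at entry |
|---|---|
| No chest pain in past 8 h | Yes, exclusion 1 |
| Arrhythmia / ECG change | Partly, exclusion 2 |
| No decompensation symptoms | Only through general 24 h stability |
| Heart rate, blood pressure, saturation limits | None |
| No further troponin rise | None |
| PLR positive | None; stated for patients already in CR |

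**2. Reproduce the plan's figure.** Inputs from Sample Size: α = 0.01, β = 0.1, SPPB 6.0 ± 2.8 at baseline and 8.3 at 3 months in the CR group, 6.9 at 3 months in control. The formula is n = 2σ² × f(α,β)/(μ₁ − μ₂)². Taking α as two-sided, f(α,β) = (2.576 + 1.282)² ≈ 14.88.

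- Difference 2.3 (8.3 − 6.0, the change within the CR arm), SD 2.8: 2 × 7.84 × 14.88 / 5.29 = 44.1. The plan states 44.
- Difference 1.4 (8.3 − 6.9, between arms), SD 2.8: 2 × 7.84 × 14.88 / 1.96 ≈ 119, or 120 per group from the unrounded routine. This does not reproduce 44.
- Losses: 44/(1 − 0.27) = 60.3, and 44/(0.80 × 0.93) = 59.1. The plan states 60, so the whole allowance is used by drop-off and missing data.

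The illustration below therefore uses 2.3 and 2.8. Whether 2.3 is a proper planning difference is a separate matter.

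**3. Dilute.** Let f be the share of the CR arm never trained, and assume that these patients gain nothing over control. The difference becomes 2.3 × (1 − f), and

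power = Φ[2.3(1 − f)√(n/2)/2.8 − 2.576].

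For n = 44, √22 = 4.690. At f = 0 the argument is 3.853 − 2.576 = 1.277 (89.9%). At f = 10% it is 3.468 − 2.576 = 0.892 (81.4%).

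| f (assumed) | Difference | Power, n = 44, α 0.01 | n per group for 90% | Power, n = 44, α 0.05 | Power, n = 60, α 0.01 |
|---|---|---|---|---|---|
| 0 | 2.30 | 89.9% | 45 | 97.1% | 97.3% |
| 10% | 2.07 | 81.4% | 55 | 93.4% | 93.0% |
| 20% | 1.84 | 69.4% | 69 | 86.9% | 84.7% |
| 30% | 1.61 | 54.8% | 91 | 76.9% | 71.7% |

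The α 0.05 column is shown because Data Analysis tests at 0.05 two-sided. The n = 60 column is the case with no losses. If the true difference were the between-arm 1.4 (SD 2.8, n = 44, α 0.01), power would be 40.9% with no dilution and 32.1%, 24.2% and 17.5% at the three values of f.

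**4. A ratio that needs no choice of difference.** The sample size for fixed power grows by 1/(1 − f)²: 1.23, 1.56 and 2.04 at f = 10%, 20% and 30%.

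**The case against.** A check before every session is a proper safety measure, and failing it once may only delay training. Never training requires failure throughout the 5 days in patients already stable for 24 h, and the document gives no sign of how often that happens. The stated aim is CR in patients hospitalised in CICU with ADHF, not in those ready to exercise, so non-delivery analysed as randomised is arguably part of the effect sought. The article names no analysis set, which may well be in an SAP. Requiring readiness before allocation narrows the population and may slow a single-centre trial.

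Much of this stands. The per-session check should stay, f is unknown, and the absence of an analysis set from the article is not a fault. But these points do not remove the mismatch, which is in the protocol text itself. An SAP can prevent selective removal, but it cannot restore contrast lost because patients were not trained. Even if the aim is the effect of offering CR, the sample size should then anticipate non-starting.

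A reader might infer three stronger things that the document does not support:

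- That the readiness check is known to take place only after randomisation. Its first timing is not stated and the flow diagram is not available here. Only the PLR condition is explicit on this.
- That none of the readiness items is screened at entry. Chest pain within 8 h is an exclusion, and arrhythmia is partly covered.
- That the trial will be diluted by a particular amount, or that non-starters will be removed. Neither is stated.

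**Conclusion.** The point holds as a mismatch between eligibility and the conditions for starting exercise. Eligible patients can be randomised to CR and then train late or never, and no equivalent condition applies in control. The evidence is firmest for the PLR condition, which is explicitly post-randomisation, confined to CR and open-ended. For the readiness check, restriction to the CR arm follows from its link to sessions, but its order relative to randomisation is unstated.

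The size is conditional. Under the inputs that reproduce 44 per group, as-randomised power drops from 90% to about 81%, 69% and 55% if 10%, 20% or 30% of the CR arm is never trained and gains nothing. Late rather than absent training would cost less. If non-starters were removed instead, the harm would be bias of unknown size in favour of CR. This is a worthwhile, inexpensive correction; it is not evidence that the trial has failed.

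**What to change.** Reconcile Inclusion Criteria, Exclusion Criteria and Intervention as follows.

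1. Carry out the first readiness assessment in every candidate before the envelope is opened, and randomise once it is passed. Use the sponsor's own reconciled list, plus the PLR test if it remains a condition for starting. Moving the readiness list alone would leave the PLR condition able to hold back patients already allocated to CR. No threshold is proposed here.
2. Keep the per-session check in the CR arm as a delivery and safety rule, and record sessions missed or delayed with the reason.
3. Do not use exclusion 12 to remove anyone after randomisation, and analyse all randomised patients in their allocated arm.

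The cost is an amendment to the criteria and to the order of screening steps, and the PLR test would also be done in patients later allocated to control. Some patients will be randomised later or not at all, recruitment may slow, and the result will apply to CICU patients ready to start exercise. Non-starting will be reduced but not abolished, since a patient can deteriorate after allocation.

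### At Levels 3–7 the heart-rate training goal lies wholly inside the safety stop, when both are read as a rise from rest

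*Protocol article*

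**What the plan says.** Three statements in Materials and Methods, Intervention, and its Table 1 bear on heart rate during training.

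- **The stop.** The list of stopping situations begins: "Rehabilitation training will be stopped if the following situations occur: new onset arrhythmia or heart rate rise ≥20 beats per minutes". It applies to training generally. It gives no reference rate, no time window and no exception for any level.
- **The goal.** The goal row of Table 1 is labelled "Heart rate response (compared with resting heart rate"). For Levels 1 and 2 the entry is "Increase 5–15 beats per minute". For each of Levels 3, 4, 5, 6 and 7 it is "Increase 20–30 beats per minute".
- **The use of the goal.** Heart-rate response, together with the Borg and Perme scores, decides whether a patient moves to the next level.

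The pre-session check also uses the resting rate: "resting heart rate <110 beats per minute". The article does not say which rule takes precedence when the goal and the stop meet.

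**The concern.** A goal that defines adequate effort and a limit that defines unsafe effort need to be separated. Here the goal for the five higher levels begins exactly where the stop begins and runs 10 bpm beyond it.

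Three things are at stake:

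- **Safety.** The patients are in a cardiac intensive care unit with acute decompensated heart failure. A therapist who pursues the goal at Levels 3 to 7 has to disregard a written stop. The trial sets out to assess safety as well as efficacy.
- **Dose.** A therapist who obeys the stop ends training once the goal is reached. That can cut short prescribed components such as "Bedside treadmill training for 10–20 min".
- **Progression.** From Level 3 to Level 6, a heart-rate response that meets the criterion for moving up also triggers the stop. A patient kept below the stop cannot meet that criterion.

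Therapists may settle the conflict differently from one another, and the programme that is finally evaluated would then not be the one described.

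**Working it through.** The plan states no figure to reproduce here. The check compares two ranges.

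**Inputs, as a rise in bpm over the resting rate**

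- Stop S (Intervention text): a rise of 20 or more. Reading it as a rise from rest is an assumption, because the text names no reference.
- Goal at Levels 1–2 (Table 1): 5 to 15.
- Goal at Levels 3–7 (Table 1): 20 to 30. Table 1 states the resting rate as the reference for both goals.

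**Headroom = stop threshold − goal value**

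| Levels | At goal floor | At goal ceiling | Whole-number goal values that meet the stop |
|---|---|---|---|
| 1–2 | 20 − 5 = +15 | 20 − 15 = +5 | 0 of 11 (5 to 15) |
| 3–7 | 20 − 20 = 0 | 20 − 30 = −10 | 11 of 11 (20 to 30) |

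The floor of the Level 3–7 goal is caught because the stop includes 20 itself.

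**Dependence on the resting rate.** There is none, since both rules are differences from the same rate. With an assumed resting rate of:

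- 60 bpm, the Level 3–7 goal is 80–90 and the stop begins at 80;
- 80 bpm, the goal is 100–110 and the stop begins at 100 (the Level 1–2 goal is 85–95, below the same stop);
- 100 bpm, the goal is 120–130 and the stop begins at 120.

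**How far the stop would have to move, with the goal kept at 20–30**

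| Stop rule | Goal values that meet the stop |
|---|---|
| ≥20 (as written) | 11 of 11 |
| >20 | 10 of 11 |
| ≥30 | 1 of 11 |
| >30 | 0 of 11 |

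Changing the inequality sign at 20 is therefore not enough.

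**The other reading.** If the stop means an abrupt rise, or a rise from the rate already reached during exercise, the overlap cannot be computed, because the text gives neither a starting rate nor a time window.

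**The case against.** The strongest reply is that the contradiction rests on a supplied premise. Table 1 states its reference rate and the stop does not. The stop sits in the same item as new arrhythmia and ECG change, which are acute events, so it may have been meant as a sudden, unexpected rise on the monitor. A missing reference rate is also operating detail that a condensed article may leave to the full protocol.

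The sudden-rise reading cannot be excluded, but it is the weaker one. The resting rate is the only reference rate that the Intervention section and Table 1 name. Where the authors wanted a time element in the stopping list, they wrote one: the fall in stroke volume has to continue for more than 1 minute. They wrote none for heart rate. Nor is the point only an omission, because both rules are printed and on the plain reading they clash. On the other reading the stop is undefined and needs the same amendment.

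Several limits on the consequence do stand:

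- The article does not say that the 20–30 bpm rise must be sustained through the treadmill bout. A patient might be stopped at +20 and still be credited with the heart-rate criterion, so the lost dose cannot be sized.
- The number of patients who will train at Levels 3–7 in the 5 days is not given. Five of seven levels is a count of levels, not of patients.
- Obeying the stop errs on the side of caution. If it is overridden, the stops for blood pressure, oxygen saturation, stroke volume, symptoms, arrhythmia and ECG change still apply.
- The randomised comparison stays valid.

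These points limit what can be said about the effect on results. They do not make the two rules compatible.

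**Conclusion.** The concern holds. With both rules read as a rise from rest, the stop covers the whole heart-rate goal at five of seven levels (11 of 11 whole-number values, headroom 0 to −10 bpm) and none of it at Levels 1 and 2 (headroom at least +5 bpm). Nothing in the article reconciles them.

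The conclusion rests on one assumption, that the stop is measured from the resting rate. It does not depend on what that rate is. The fault lies in the definition of the intervention and its safety limit; sample size and analysis are not touched. It should be corrected before the programme is delivered as written, because at those levels a therapist cannot both train patients in the goal range and keep to the stop.

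**What to change.** Amend the Intervention text and Table 1 so that the stop and the goal name the same reference, the resting heart rate, and do not overlap. There are two ways to do this:

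1. Set the stop above each level's goal, for example more than 30 bpm over rest at Levels 3–7, keeping 20 bpm or more at Levels 1–2.
2. Keep the stop at 20 bpm or more throughout and lower the Level 3–7 goal below 20 bpm.

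Which limit is safe is a clinical decision for the investigators. If an abrupt rise was intended, the text should say so, with the starting rate and the time window. Therapists should be retrained on the amended rule.

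The same amendment can correct a clerical slip in the pre-session checklist, where the item on new arrhythmia and ECG changes has lost its negation. That slip carries no weight in this finding.

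The cost is one clinical decision, a short amendment and brief retraining. Sample size and analysis do not change.

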## Materials and Methods

### Study Design

This is a single-center, randomized controlled, single-blind clinical trial, which is designed to evaluate the efficacy and safety of CR in patients hospitalized in CICU with ADHF. This study protocol follows the principles of the Standard Protocol Items: Recommendations for Intervention Trials (SPIRIT) statement (18). This study has been approved by the Ethics Committee of Xiamen Cardiovascular Hospital of Xiamen University (approved number: 2021YLK6) and registered at Chinese Clinical Trial Registry (registration number: ChiCTR2100050151).

This study includes a 5-day intervention period and a 6-month follow-up period. A total of 120 patients hospitalized in CICU with ADHF will be randomly assigned to the two groups with a 1:1 ratio. Participants will receive tailored and progressive CR intervention or attention control. Clinical outcome evaluation will be conducted before and after intervention and at 6 months. The flow diagram of the study protocol is outlined in Figure 1.

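### The in-session blood pressure stop rule has no lower limit, so a patient cleared at 90–129 mmHg systolic can fall below 90 mmHg without meeting it

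*Protocol article*

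**What the plan says.** Under Intervention, the protocol article requires a clinical evaluation before every training session. Among the conditions for going ahead is "resting blood pressure (BP) 90–150/60–100 mmHg and blood oxygen saturation (SaO_2_) ≥95" per cent. The systolic window at rest is therefore 90 to 150 mmHg.

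The same section then lists the events that end a session in progress. The only blood pressure item is "systolic BP drops or rises more than 40 mmHg". The other items are new arrhythmia, a heart rate rise of at least 20 beats per minute, dynamic ECG change, saturation below 95%, "a continuous downward trend in SV more than 1 min", and symptoms of exercise intolerance.

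Pressure is measured during training: "A rehabilitation therapist will closely monitor the ECG, BP", together with saturation and impedance cardiography. No absolute systolic limit for use during training appears in the stop list, in Table 1 or elsewhere in the article.

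**The concern.** The stop criterion is purely a change score. A change score protects least where the starting value is lowest: the same 40 mmHg fall takes a patient from 150 to 110, or from 90 to 50. Followed exactly, the blood pressure rule lets training continue at pressures that would have barred the same patient from starting.

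Safety is a stated aim, since the trial is "designed to evaluate the efficacy and safety of CR in patients hospitalized in CICU with ADHF". Participants are in a cardiac intensive care unit with acute decompensated heart failure and were in NYHA class III or IV at admission. Table 1 asks them to change position, for example "Sitting at the edge of the bed 5 min, 2 times per day" from Level 3, with standing, stepping and transfer to a chair from Level 4. Pressure can fall during such moves.

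**Working it through.** The article states no figure to reproduce here. The check applies the stop rule to every systolic value that the entry rule admits.

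**Inputs**
- Resting systolic value *s* that permits a session: 90 to 150 mmHg (Intervention, pre-session evaluation).
- Blood pressure stop: a systolic change of more than 40 mmHg (Intervention, stop list).
- Assumption: the change is measured from the pre-session resting value. The article does not name the reference.

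**Current rule.** A fall of exactly 40 does not exceed 40, so the lowest systolic value that fails to meet the criterion is *s* − 40. With an added floor of 90 it would be max(*s* − 40, 90), and the permitted fall would be min(40, *s* − 90).

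| Start (mmHg) | Lowest value not meeting the current criterion | Lowest value with a floor of 90 | Permitted fall with a floor of 90 |
|---|---|---|---|
| 90 | 50 | 90 | 0 |
| 100 | 60 | 90 | 10 |
| 110 | 70 | 90 | 20 |
| 120 | 80 | 90 | 30 |
| 129 | 89 | 90 | 39 |
| 130 | 90 | 90 | 40 |
| 150 | 110 | 110 | 40 |

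**Exposed band.** *s* − 40 < 90 requires *s* < 130, so the band is 90–129 mmHg.
- Whole-mmHg values in the band: 129 − 90 + 1 = 40.
- Whole-mmHg values admitted at entry: 150 − 90 + 1 = 61.
- Share of the entry range: 40/61 = 65.6%.

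These are limits of the blood pressure criterion taken alone, not of the whole stop list.

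**The case against.** **Other safeguards exist.** Before exercise, the patient must meet "Clinical stability has been achieved for 24 h after optimizing treatment", pass the pre-session evaluation and pass the passive leg raise gate ("Patients randomized to the CR group will start the exercise program if the PLR test is positive"). During exercise, a therapist is at the bedside, and a sustained fall in stroke volume, a heart rate rise, an ECG change, desaturation or symptoms each stop the session. This largely stands: these triggers would end many sessions in which pressure fell badly. But the first three act before training rather than during it, and none of the rest is tied to a pressure. The stroke volume trigger is the best backstop, yet it needs a continuous fall lasting more than 1 minute. The heart rate trigger is hard to rely on, because a rise of 20–30 beats per minute is Table 1's own goal at Levels 3–7. The symptom list is open-ended, but its named examples do not include dizziness or syncope.

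**A reader might infer that the protocol contradicts itself**, because saturation has the same limit for entry (at least 95%) and for stopping (below 95%) while blood pressure does not. The documents do not support that. Heart rate is handled as blood pressure is: an absolute limit at entry (below 110 beats per minute) and a relative rise as the stop. Nothing says that entry and stop limits must match, so the saturation rule is no evidence of inconsistency.

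**The phrase could be read differently**, as any drop at all or a rise above 40 mmHg, which would remove the gap. The ordinary reading applies the 40 mmHg to both verbs, and nothing in the article favours the other.

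**The article is condensed.** A full protocol or therapist manual might set a floor. That lowers confidence that the trial lacks one. It does not change what the published stop list, given in numeric detail, says.

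**Conclusion.** The point holds as a safety gap in a stated rule and is worth a cheap correction. The blood pressure criterion alone does not stop a patient cleared at 90–129 mmHg from falling below 90, and it tolerates 50 mmHg from a start of 90.

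Two larger readings should be resisted. The 65.6% is a share of the admitted range, not of patients: the article gives no distribution of entry pressures, so neither the number exposed nor the frequency of such falls can be estimated. Nor does the figure of 50 mmHg predict that anyone will be trained at that pressure, since other triggers would often act first.

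The conclusion rests on the ordinary reading of the criterion, on the pre-session resting value as its reference, and on there being no floor in a document that is not shown. It concerns only the lower systolic limit. No effect on an endpoint or analysis is claimed.

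**What to change.** In the stop list under Intervention, replace the blood pressure item with: *systolic BP below 90 mmHg (confirmed on an immediate repeat reading), or a fall or rise of more than 40 mmHg from the pre-session resting value*.

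The default of 90 mmHg is the protocol's own entry limit. The repeat reading avoids stopping on a single low value or a brief dip on a change of position. Naming the reference value also settles how the 40 mmHg is measured and removes the ambiguity about a drop.

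The cost is one line and a therapist briefing. Pressure is already monitored at the bedside, so the only extra work is one repeat reading when a value is below 90.

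The downside is earlier stopping in patients who start near 90 mmHg: at a start of 90, a confirmed 89 ends the session. If the investigators find that too strict, a somewhat lower stated floor, chosen on clinical grounds, would still bound the fall. Purely as an illustration, a floor of 80 mmHg (not a figure from the article) permits a fall of min(40, *s* − 80), which is 10 mmHg from a start of 90 and 20 from 100.
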